### Interventions

The interventions in this study will take place on 3 consecutive days each week for 4 weeks. The study flowchart (Figure 2) provides a detailed overview of participant flow through the clinical trial.

**Figure 2 figure2:**
[figure not shown]
Flowchart of the study. CIMT: constraint-induced movement therapy; FMA-UE: Fugl-Meyer Assessment for upper extremity; MAL: Motor Activity Log; NMES: neuromuscular electrical stimulation; UPSET: Upper Limb Self-Efficacy Test; WMFT: Wolf Motor Function Test.

#### CIMT Group

In the CIMT group, the shaping practice of CIMT will perform the following: picking up a cup from the table, taking it to the mouth, and putting it back; writing letters or drawing a circle; picking up an object (a pen or pencil) and transferring from right to left on the table; taking the hand from the lap to the head and sliding it from the front to the back; taking the hand to the nose; and putting and removing shoes. These 6 tasks will be performed 50 times, totaling 300 repetitions per session. The tasks were developed following a protocol outlined in a previous study [29].

Participants will complete hour-long CIMT sessions 3 times per week for 4 weeks, aiming to perform the 300 task repetitions within each session. This repetition target is supported by evidence from previous studies [30-32], showing that ≥300 daily repetitions can drive motor function recovery and can be achieved within 1 hour of focused practice. Structured progression criteria will adjust the tasks throughout the intervention to standardize the repetition counts while accommodating individual capacities.

Participants in the CIMT group will wear a padded or oven mitt on their unaffected UE for 90% of waking hours, 3 days per week, over the 4-week intervention period. On the basis of studies by Abdullahi [29], Wolf et al [33], and da Silva et al [34], this constraint protocol aims to promote intensive use of the affected limb during daily activities.

The selection of mitts was based on affordability, accessibility, and ease of maintenance considerations. Adherence to the constraint protocol will be monitored through participant self-report logs, verified by caregivers when possible, and direct therapist observations during treatment sessions.

Table 1 outlines the CIMT intervention framework, detailing the types of tasks, repetitions, sessions per day, and duration of task practice.

**Table 1 table1:** Characteristics of the constraint-induced movement therapy intervention.

Task	Task repetitions per session, n	Sessions per day, n	Days per week, n	Weeks, n
Picking up a cup from the table, taking it to the mouth, and putting it back	50	1	3	4
Writing letters or drawing a circle	50	1	3	4
Picking up an object (pen or pencil) and transferring it from right to left on the table	50	1	3	4
Take the hand from the lap to the head and slide it from the front to the back	50	1	3	4
Taking the hand to the nose	50	1	3	4
Putting on and removing shoes	50	1	3	4

#### CIMT and NMES Group

Participants in the CIMT+NMES group will perform functional tasks similar to those in the CIMT group, with the addition of NMES delivered via a biofeedback electrical stimulator. During NMES sessions, participants will be seated with their paretic arm resting at their side and forearm pronated. Two stimulating electrodes will be placed over the extensor carpi radialis muscle belly. Participants will be instructed to relax the paretic arm while stimulation intensity is adjusted to elicit a sustained muscle contraction, known as a tetanic contraction, producing 20° to 25° of wrist extension without pain. NMES will be administered for 20 minutes per day, 3 days per week, over the 4-week intervention period.

NMES will be applied immediately following the completion of each CIMT session. This sequencing optimizes neuromodulatory effects while preserving volitional movement patterns during functional tasks [35,36]. By delivering NMES after the CIMT protocol, this approach allows for muscle activation without the influence of fatigue, potentially enhancing the therapeutic benefits of the combined intervention.

The NMES intervention will incorporate the use of an NMES stimulator (Balego EMS Digital Neuromuscular NMES Stimulator OTC) to deliver symmetric biphasic pulses. The stimulator will be set at a 35- to 50-Hz frequency with a 200- to 250-microsecond pulse width. Intensity will be individually adjusted to produce visible muscle contraction without discomfort, and electrode placement will target the wrist and finger extensor muscles.

#### Control Group

The control group will receive conventional rehabilitation therapy following a standardized protocol developed from established clinical guidelines [37,38]. This evidence-based approach ensures that participants in the control group receive consistent, high-quality care representing current best practices in stroke rehabilitation while maintaining a clear distinction from the experimental interventions.

Each 60-minute control session follows a structured format comprising 4 distinct therapeutic components. Sessions commence with 15 minutes of passive and active range of motion exercises systematically targeting all UE joints. Therapists guide participants through standardized movement sequences encompassing shoulder flexion, abduction, and rotation; elbow flexion and extension; and comprehensive wrist and finger movements. Each movement follows predetermined repetition counts with explicit progression criteria based on individual functional capacity.

The second component consists of 20 minutes of neurodevelopmental facilitation techniques. This segment incorporates weight-bearing activities performed in specified positions for predetermined durations, bilateral integration tasks systematically selected from our standardized task bank, and tone normalization techniques following established therapeutic principles. Task selection follows a structured decision algorithm that ensures consistency across therapists while permitting appropriate clinical judgment for individual participant needs.

Functional task practice occupies the subsequent 20 minutes, emphasizing activities of daily living relevant to participants’ rehabilitation goals. Task difficulty is systematically graded according to the Motor Assessment Scale scores, with compensatory strategy training incorporated when standardized criteria indicate clinical necessity. Each session concludes with 5 minutes of fine motor activities, including standardized pegboard tasks and grip strength exercises using specified resistance parameters.

All participating centers will receive identical therapy kits containing standardized materials to eliminate equipment-related variability. We have developed a comprehensive therapy manual featuring detailed photographic demonstrations, step-by-step instructions, and decision algorithms guiding exercise selection and progression. We will systematically review individual participant progress in weekly case discussions and ensure protocol adherence while maintaining necessary clinical flexibility within our structured therapeutic framework.

The principal researcher and health care professionals will administer therapy sessions in all groups. To ensure rigorous data collection and participant safety, all participants will have standardized logbooks to document their therapy sessions. The research team will monitor each participant’s adherence to the assigned intervention and track any potential adverse events, such as muscle cramps or soreness, every week.

For participants with cognitive or motor limitations that affect their ability to maintain the logbooks independently, assistance will be provided by caregivers or trained research assistants. All instances of such assistance will be carefully recorded to preserve data integrity and allow for appropriate analysis and interpretation of the results.

This multimodal monitoring approach, incorporating both self-report and direct observation, is designed to comprehensively assess adherence while accommodating the potential functional limitations of the stroke survivor population. By systematically tracking adherence and adverse events, the study aims to ensure participant safety, maximize data quality, and ultimately enhance the validity and generalizability of the findings.

Table 2 outlines the framework of all study interventions, including a comparison between the 3 groups.

**Table 2 table2:** Framework of interventions: comparison between groups.

Characteristics	CIMT^a^ group	CIMT+NMES^b^ group	Control group
Total duration (min)	60	CIMT: 60; NMES: 20	60
Delivery	Researchers and health care professionals	Researchers and health care professionals	Researchers and health care professionals
Content	6 tasks of CIMT (50 repetitions for each task)	6 tasks of CIMT (50 repetitions for each task) + biofeedback electrical stimulator	Neurodevelopmental techniques emphasizing the functional task practice
Location	1 NASAM^c^ center	1 NASAM center	1 NASAM center
Frequency	1 session per day for 3 consecutive days a week for 4 weeks	1 session per day for 3 consecutive days a week for 4 weeks	1 session per day for 3 consecutive days a week for 4 weeks

^a^CIMT: constraint-induced movement therapy.

^b^NMES: neuromuscular electrical stimulation.

^c^NASAM: National Stroke Association of Malaysia.

#### Intervention Fidelity Monitoring

To ensure consistent intervention delivery across all sites and maintain protocol adherence, we have developed a comprehensive fidelity monitoring system based on the National Institutes of Health Behavior Change Consortium recommendations [39]. This multicomponent framework integrates standardized documentation, independent quality assurance, and technology-enhanced monitoring to maintain treatment integrity throughout the trial.

Our monitoring protocol incorporates standardized treatment fidelity checklists tailored explicitly to each intervention arm. These checklists document critical elements for every session, including exercise parameters, constraint application procedures, and NMES settings. Therapists will complete session-specific adherence forms immediately following each treatment, recording quantitative data on task repetitions completed, constraint wear time achieved, and stimulation parameters used. In addition, therapists will complete weekly self-assessment rubrics designed to promote reflective practice and facilitate early identification of protocol deviations.

Independent quality assurance measures will strengthen monitoring objectivity. The research coordinator will conduct biweekly observations across all sites using structured evaluation forms to assess protocol adherence systematically. An independent assessor uninvolved in the treatment delivery will randomly audit 20% of all sessions to ensure unbiased evaluation. With participant consent, we will video-record one session weekly per therapist for comprehensive offline analysis, enabling a detailed review of intervention technique and adherence verification.

Technology integration will enhance monitoring precision through automated data collection. NMES devices will generate electronic logs that objectively track all stimulation parameters, providing verifiable records of treatment delivery. We will systematically cross-validate participant-maintained logbooks with therapist records to verify reported constraint wear time and home practice completion. Weekly research team meetings will review aggregated adherence data, allowing prompt identification and resolution of any protocol deviations. This integrated monitoring approach balances rigorous quality control with practical feasibility, combining self-report measures, direct observation, and objective technological data to maintain optimal treatment fidelity throughout the trial.

### Outcome Measurements

#### Feasibility

The feasibility of all interventions will be assessed based on the measures described in subsequent sections.

#### Patient Acceptance

Stroke survivors’ perceptions of the therapy will be evaluated through a posttrial question asking, “What do you think about this therapy?” Responses will be categorized as positive or negative and analyzed descriptively.

#### Adherence Rate

Adherence will be measured as the percentage of prescribed therapy sessions completed (out of 12). Data will be collected from participants’ logbooks.

#### Adverse Effects

Exercise-related adverse effects, such as strain, cramps, and muscle soreness, will be monitored weekly and evaluated in posttrial assessments.

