**Exclusion criteria**
Sensory loss score of ≥2 on the National Institutes of Health Stroke Scale sensory item. Such impairments can affect the ability to use the upper extremity in everyday activities [26]Patients with pacemakers or tumors owing to their contraindication to the implementation of the neuromuscular electrical stimulation [27,28]

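### The evaluated adverse-effect outcome covers exercise-related effects only, narrower than the weekly adverse-event tracking, so events from stimulation or the mitt have no stated place in it

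*Protocol article*

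**What the plan says.** Two places in the protocol article set the scope of adverse-event work.

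- **Outcome Measurements, Adverse Effects** (a feasibility measure): "Exercise-related adverse effects, such as strain, cramps, and muscle soreness, will be monitored weekly and evaluated in posttrial assessments".
- **Control Group, closing paragraphs**, which despite the heading apply to every participant: the research team will "track any potential adverse events, such as muscle cramps or soreness, every week". The purpose follows: "By systematically tracking adherence and adverse events, the study aims to ensure participant safety".

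The Feasibility section introduces the first of these with "The feasibility of all interventions will be assessed based on the measures described in subsequent sections".

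Two treatment components bear on the point.

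- **CIMT and NMES Group:** "NMES will be administered for 20 minutes per day, 3 days per week, over the 4-week intervention period". It is given straight after the CIMT session with the arm at rest, and "Intensity will be individually adjusted to produce visible muscle contraction without discomfort". The exclusion criteria rule out "Patients with pacemakers or tumors owing to their contraindication to the implementation of the neuromuscular electrical stimulation".
- **CIMT Group:** a mitt is worn "on their unaffected UE for 90% of waking hours", three days a week for four weeks. The section on the combined arm says that its tasks are similar to those of the CIMT arm; it does not mention the mitt.

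**The concern.** In the Adverse Effects definition the words that introduce the examples leave the list open, but only among effects that are exercise-related. That qualifier decides what enters the outcome.

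Active practice of some kind is part of all three arms. Stimulation of a resting arm and hours of mitt wear outside the session are not exercise in the ordinary sense, and the control arm has neither. A harm measure limited to exercise therefore describes best what the arms share and describes least well where they differ.

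At stake is the completeness of the harm summary. If the Adverse Effects section is followed as written, a stimulation-site reaction or a mishap while wearing the mitt could sit in the weekly records and be absent from the reported outcome. A reader of the results could then take a short list of adverse effects as evidence that the added components were well tolerated, when events of that kind were never eligible for the list.

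**Working it through.** The plan gives no figure on this point to reproduce, so the check is mainly a comparison of texts.

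**1. Scope of each statement**

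| | Weekly monitoring (end of Control Group section) | Evaluated outcome (Adverse Effects) |
|---|---|---|
| Events covered | any potential adverse event | exercise-related effects |
| Examples | cramps, soreness | strain, cramps, soreness |
| Frequency | weekly | weekly, plus post-trial evaluation |
| Role | participant safety and data quality | feasibility measure |

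The second scope is a subset of the first. The article does not say which governs the report.

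**2. Is there another outcome for the events in the gap?**

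- *Mitt:* Constraint Adherence measures the share of target hours worn. It records no harm.
- *NMES:* Intervention Fidelity Monitoring records settings through checklists and device logs. The CIMT and NMES Group section sets intensity so as to avoid pain and discomfort. None of this is a harm outcome.
- *Remaining feasibility measures:* patient acceptance, session adherence and repetition adherence. A participant might mention discomfort in answer to the acceptance question, but answers are classed only as positive or negative.

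So no listed outcome names a harm of stimulation or of the mitt.

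**3. How many participants have an exposure outside the literal definition?**

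Input: 42 participants, 14 per arm (Sample Size Calculation).

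- NMES: one arm, 14 of 42 = 33%.
- Mitt: stated for the CIMT arm, 14 of 42 = 33%. If the combined arm also wears it, 14 + 14 = 28 of 42 = 67%.
- Control: 0 of 14 for both.

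**4. Could the size in events be computed?**

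No, because the article gives no event rate. For scale only, take assumed true rates p of 5%, 10% and 20% for some stimulation-related event, independent between participants. The chance that at least one of 14 participants has it is 1 − (1 − p)^14:

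- p = 5%: 1 − 0.95^14 = 0.51
- p = 10%: 1 − 0.90^14 = 0.77
- p = 20%: 1 − 0.80^14 = 0.96

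If every event is eligible and none is seen in 14 participants, the one-sided 95% upper limit for the rate is 1 − 0.05^(1/14) = 19.3%. An arm of this size thus gives only coarse information on harms even with full capture. If such events are not eligible for the outcome, a zero there gives no information on them at all.

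**The case against.** The strongest reply is that nothing is lost. The monitoring rule covers any potential adverse event for every participant, so a skin reaction or a mitt-related event would be recorded each week. Tracking everything and evaluating a subset are compatible, and the near-identical examples suggest that one weekly process is described twice in loose wording. The named effects, cramps and soreness, can also follow from stimulation strong enough to hold a muscle contraction, so part of the NMES burden may be captured whatever the label says. A journal article also leaves event definitions, form items and tables to the full protocol.

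Much of this stands, and it limits the point. Several stronger readings that a reader might infer are not supported:

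- *That the two sections contradict each other.* They differ in scope; both can be carried out.
- *That stimulation or mitt events go uncollected.* The monitoring rule covers them. What they lack is a stated place in the evaluated outcome.
- *That a safety comparison between arms is biased.* The article describes no such comparison; adverse effects are listed under feasibility.
- *That unblinded staff would decide which events are exercise-related.* No relatedness procedure is described and no evaluator of adverse effects is named. Therapists and patients are unblinded, but Assessment of Outcomes gives the postintervention assessments to a blinded assessor, and whether that person also evaluates adverse effects is not stated.
- *That 28 participants certainly wear the mitt.* Wear is stated for the CIMT arm only.

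The appeal to condensation does not remove the rest. The point concerns a qualifier that the article states, not a detail that it leaves out. A wider definition in a fuller document would still need to be reconciled with this one.

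**Conclusion.** The point holds as a mismatch of scope, and it is minor. The outcome that is evaluated is narrower than the events that are tracked, and the gap falls on exposures that the control arm does not have. That sits poorly with the stated aim of assessing the feasibility of every intervention.

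The conclusion rests on reading the exercise qualifier literally, since the article does not define it. If the investigators meant it loosely, only the wording needs repair. The exposure counts in the working assume that recruitment meets the planned arm sizes; the effect on reported harms cannot be estimated from the document. The efficacy outcomes, their analysis and the sample size are unaffected.

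**What to change.** Reword the Adverse Effects outcome so that its scope equals that of the weekly monitoring rule: all adverse events of any cause, collected weekly on the same form in all three arms and summarised descriptively by arm. State that events linked to stimulation or to mitt wear are included, and give each a line on the form. Record judged relatedness in a separate field, so that it describes an event and does not decide whether the event counts. State also whether the combined arm wears the mitt, so that the number exposed is clear when the tables are read.

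The cost is a few more lines on the weekly form and slightly longer tables. Weekly tracking is already planned, so no visit is added, and no treatment, schedule or clinical rule changes.

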#### Repetition Adherence

The number of task repetitions will be calculated. If a participant is unable to complete all repetitions, the number of completed repetitions will be recorded, and the percentage of task completion will be calculated for adherence assessment. Therapists will adapt task complexity to maintain appropriate challenges while enabling maximum quality repetitions within individual capacity. This ensures standardized assessment while accounting for individual variability.

#### Constraint Adherence

Adherence to the constraint protocol will be monitored using daily logbooks for self-reported mitt wear, caregiver confirmation when available, and weekly therapist check-ins. The percentage of target constraint hours achieved will be calculated as a feasibility outcome. This multimodal approach ensures a comprehensive assessment of adherence, informing the interpretation of study outcomes and guiding future CIMT intervention design.

#### Intended Outcome Measures

##### Overview

Table 3 illustrates the framework for all study outcomes, including the instruments used to assess each variable. The details of the intended outcome measures for the interventions in the main study (RCT) are provided in subsequent sections.

**Table 3 table3:** Framework of the study’s outcome measures and instruments.

Variables	Instruments
Motor impairment	Fugl-Meyer Assessment for upper extremity
Motor function	Wolf Motor Function Test
Perceived motor function	Motor Activity Log
Upper limb self-efficacy	Upper Limb Self-Efficacy Test

##### Motor Function Subscale of the Fugl-Meyer Assessment for Upper Extremity

The Fugl-Meyer Assessment (FMA-UE) will be used to assess motor function, coordination, and speed of the affected extremity, hand, and wrist after stroke. The FMA-UE is a well-established and reliable measure with excellent internal consistency [40,41]. In addition, it has been reported as a reliable and valid measure of poststroke upper limb motor impairment [42]. It assigns scores from 0 to 2 (0=cannot perform, 1=performs partially, 2=performs fully), with a total possible score of 66.

##### Wolf Motor Function Test

The Wolf Motor Function Test will assess the speed and accuracy of single- and multijoint movements and functional tasks of the UE. This test has been reported as a reliable and valid measure [43]. It includes 17 items, each rated on a scale from 0 to 5, where higher scores indicate greater ability (0=no ability and 5=normal ability, representing the ability to perform tasks with the same efficiency and coordination as an individual with no motor impairment).

